- Develops and implements intervention plan to assist patients and families in accessing, seamless, coordinated care based on identified needs, e.g. timely appointments, transportation services, referral to social services, etc.
- Participates with the primary care and cancer team.
- Follows up with patients who missed appointments to assure all barriers to care are addressed as needed.
- Accompanies patient and family to appointments when necessary, serving as a “cultural translator” and patient advocate when appropriate.
- Serves as a liaison between the community and cancer centers/specialists.
- Provides emotional and spiritual support as needed to patient and family.
- Provides (makes) appropriate referrals and linkages to cancer center and community resources; assists patients with securing financial benefits and entitlements.
- Utilizes interventions and strategies that are appropriate to the population, i.e., considering culture, literacy, language, age and gender.
- Evaluates interventions and outcomes continuously and then reformulates plan of action based on responses and needs.

While protocols will be established to guide the navigator in this systems role, there is also a keen focus on client-centered care. In summary, the navigator serves as a constant, that is, a person who consistently guides the patient through the system. The navigator is someone who can piece together complex information in logical and easy-to-understand ways to achieve timely and appropriate access to vital cancer care.

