**D.4.7.b Statistical Analysis and Study Power**

The statistical analyses will focus on those subjects receiving an abnormal or suspicious mammogram (BIRAD 0, 4, or 5) and those with abnormal FOBTs or abnormalities detected on sigmoidoscopy (see D.2.1). Those in the Navigator intervention groups will be compared to those in the control groups with respect to two outcomes. For patients with breast or colorectal abnormalities, the primary outcome will be time from detection of abnormality to definitive diagnosis, measured as a continuous variable. In addition, we will assess the proportion of patients who successfully complete an appropriate diagnostic evaluation. The records of each subject with such an indication for follow-up will be examined as described in D.3.3.

Study power is based on the following factors. The primary endpoint is ‘Length of time’ (LOT=time from screening to definitive diagnosis). Suppose LOT follows a normal distribution (mean=30 days, “std” = standard deviation). Then, to detect the difference in LOT between two groups (navigator versus control groups), a two-sample t-test will be used. The required minimum sample size to achieve 80% statistical power is calculated based on the t-test and illustrated in Figure 1.

For example, group sample sizes of 29 and 29 (total 58) achieve 80% power to detect a difference of 10 days between the null hypothesis that both group means are 30.0 and the alternative hypothesis that the mean of Navigator group is 20 days with estimated group standard deviations of 15.0 each and with a significance level of 0.05 using a one-sided two-sample t-test. However, to detect a difference of 5 days with the same standard deviation 15.0 between the two groups, one would need at least 112 samples for each group (total 224).

Figure 1. Required sample sizes for each group based on the expected mean of navigator group by the standard deviation. For the control group, the mean value of LOT was set up as 30.0. The standard deviations for both groups are assumed to be equal. α=0.05 (one sided: mean 1 > mean 2).

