Although we do not expect attrition of clinics, we have assessed power the possibility of between 6 and 8 participating clinics enrolling about 100 subjects each (a total of 600 - 800 subjects). Depending on the intracluster correlation coefficient (ICC) and the design effect, however, there may be effectively fewer subjects enrolled in this study from a statistical perspective. Assuming the intracluster correlation coefficient (ICC) to be in the range of 0.01 through 0.04, the effective sample sizes will be obtained as follows,

| # of total clinics | Actual Sample Sizes | ICC | Design Effect | Effected Sample Sizes |
| --- | --- | --- | --- | --- |
| 8 | 800 | 0.01 | 1.99 | 402 |
| 6 | 600 | 0.01 | 1.99 | 302 |
| 8 | 800 | 0.02 | 2.98 | 268 |
| 6 | 600 | 0.02 | 2.98 | 201 |
| 8 | 800 | 0.04 | 4.96 | 161 |
| 6 | 600 | 0.04 | 4.96 | 121 |

Therefore, given our expected sample sizes (600-800 subjects) even under the most conservative conditions (low design effects or ICC values, and relatively high population standard deviation), we will expect the desired statistical power will be achieved.

We will also conduct a number of secondary analyses in an exploratory fashion. For those with a suspicious screening result, we will compute the Kaplan-Meier curves for time from the suspicious result to definitive diagnosis (positive or negative) for each randomized arm. For those with positive diagnoses, we will compute Kaplan-Meier curves for time to onset of therapy for each randomized arm from both suspicious screening result and definitive diagnosis. In each case, we will estimate the standard error of these estimates with Greenwood’s formula and produce 95% confidence bands for these curves using the method of Hall and Wellner. The log rank test will be used to compare the two randomized groups. These comparisons will be at the two-sided 0.05 significance level.

Degree of adherence to NCCN standards will be assessed by an independent assessor blinded with respect to randomized arm and rated as 1 = complete adherence, 2 = substantial adherence, or 3 = poor adherence. The two randomized arms will be compared with respect to these adherence ratings using Wilcoxon’s Rank Sum Test.

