All comparisons of the Navigator Program to the control group will be based on the ‘intent to treat principle’. That is, all patients who give consent and are registered on the study will be analyzed according to the randomized group assignment without regard to their degree of participation. Additional analyses, limited to those assigned to the Navigator Program, will explore the effects of degree of participation on the study endpoints. These analyses will incorporate participation ratings of 0 = no participation, 1 = some participation, 2 = substantial or complete participation that will be given to each patient by the Navigator assigned to that patient. Although outcome data on those patients refusing to consent in the study will not be available, we will compare those refusing to those agreeing to participate with respect to demographic variables such as age, race, gender, etc.

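### The exploratory test of time from suspicious result to therapy uses only patients who later get a positive diagnosis, a set that navigation can change, so it does not compare the randomized arms

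*Protocol*

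**What the plan says.** Protocol D.4.7.b introduces this block as secondary: "We will also conduct a number of secondary analyses in an exploratory fashion". Everyone with a suspicious result contributes to the curve for time to definitive diagnosis, whether positive or negative. The therapy curves are narrower: "For those with positive diagnoses, we will compute Kaplan-Meier curves for time to onset of therapy for each randomized arm". They run on two clocks, "from both suspicious screening result and definitive diagnosis". Then: "The log rank test will be used to compare the two randomized groups", and "These comparisons will be at the two-sided 0.05 significance level".

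The same section puts all navigator-versus-control comparisons under intent to treat and explains that "all patients who give consent and are registered on the study will be analyzed according to the randomized group assignment". It states no exception for the therapy curves.

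Two other places show that reaching a diagnosis is itself a target of the program. D.4.7.b adds a second outcome: "we will assess the proportion of patients who successfully complete an appropriate diagnostic evaluation". D.4.4 lists among the navigator's tasks: "Follows up with patients who missed appointments to assure all barriers to care are addressed as needed".

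**The concern.** On the clock that starts at the suspicious result, a patient belongs to the analyzed set only because of something that happens later. A patient with cancer who is never worked up is not counted as untreated; that patient disappears from the comparison. If navigators bring such patients to diagnosis late, they enter the navigated curve with long times, while their counterparts at control clinics are absent. The navigated curve then looks slower because more patients were reached.

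The hypothesis in section A covers delay in the delivery of cancer care as well as in diagnosis, and this block holds the only stated between-arm test of time to treatment. D.5.1 says that dissemination will be informed by findings on timeliness of care. A masked benefit, or a significant result in the wrong direction, could mislead that step.

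**Working it through.** **1. The plan's own figures.** The protocol states no event count or power for the therapy comparison. Its only delay figures are those for the primary endpoint: mean 30 days, SD 15, navigated mean 20 days, one-sided 0.05, 80% power. For a 10-day difference, n = 2 × (1.645 + 0.842)² × 15² / 10² = 27.8, so 28 per group by the normal approximation. The stated 29 has exact t-test power of 80.6%. For 5 days the formula gives 111.3, so 112 per group, as stated. These figures reproduce, and the 30-day mean, SD 15 and the 5- and 10-day speed-ups are used below.

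**2. Direction, in closed form (assumed values).** Prompt cancers take a mean of 30 days to diagnosis and 30 more to therapy in both arms, 60 in all. Hard-to-reach cancers, when diagnosed, take 120 to 330 days (mean 225) plus 30, so 255. Control diagnoses none of the hard-to-reach. Navigation slows nobody.

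- 20% hard-to-reach, three quarters of them diagnosed under navigation (undiagnosed 20% v 5%): navigated mean (0.80 × 60 + 0.15 × 255) / 0.95 = 91 days, against 60 in control. Navigation looks 31 days worse, although 95% rather than 80% of cancers reach diagnosis.
- Undiagnosed 10% v 3%: (0.90 × 60 + 0.07 × 255) / 0.97 = 74 days, against 60. Navigation looks 14 days worse.

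**3. Rejection rates in the same model.** Simulated two-sided 0.05 log-rank tests on the positive-only set, with 60 cancers per arm unless stated:

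| Undiagnosed, control v navigator | Speed-up in prompt patients | Significant against navigation |
|---|---|---|
| 20% v 5% | none | 66% |
| 20% v 5%, 20 cancers per arm | none | 24% |
| 20% v 5% | 30 to 20 days | 8% |
| 10% v 3% | none | 22% |
| 10% v 3% | 30 to 25 days | 4% |
| 10% v 3% | 30 to 20 days | 0.1% |

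In the last row about one trial in ten is significant in favor of navigation. Sixty cancers per arm is 120 in all, or 15% of 800 subjects and 20% of 600. Twenty per arm is 5% of 800.

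**4. A second model that includes patients without cancer (assumed values).** In the main case, 60% of patients are easily worked up (mean 30 days in both arms). Of the other 40%, 20% in control and 80% under navigation complete the work-up, with means of 150 and 120 days. Diagnosis to therapy averages 30 days in both arms. Follow-up is 12 months, there is no clinic effect, and 10% of 1,600 subjects have cancer (1,600 is the Phase II maximum in E.1.1). The all-subject test keeps every patient in the denominator.

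| Case | Positive-only: against / in favor | All-subject: against / in favor |
|---|---|---|
| Main case | 37% / 0% | 0% / 39% |
| Main case, 800 subjects | 25% / 0.5% | 0% / 23% |
| Modest completion effect (80% easy; hard-to-reach 30% to 60%) | 6% / 0.2% | 1% / 6% |
| Pure acceleration, equal completion | 0% / 41% | 1% / 4% |
| No effect | 3% / 4% | 2% / 1% |

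In the main case, 91% v 68% of true cancers start therapy by 12 months, yet median time to therapy in the positive-only set is about 70 days (navigator) v 59 (control). With yields of 5% to 20% and 800 to 1,600 subjects, results against navigation run from 13% to 64% in the main case and from about 5% to 12% with the modest effect, against a nominal 2.5%.

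Suppose navigation also speeds diagnosis (easy patients 30 to 20 days, hard-to-reach 150 to 100). With 160 cancers, the positive-only test is then 8% against and 0.5% in favor. Had every cancer been observable and kept, 91% of trials would have favored navigation. The benefit is mostly hidden rather than reversed.

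**5. The other clock.** Counted from diagnosis, the mean test statistic stayed near zero in the cases checked. That is because diagnosis-to-therapy time was set equal for all patients.

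**The case against.** - **Status.** The analysis is labeled exploratory, and the primary outcome is time to definitive diagnosis. This stands. A reader might infer that the trial could conclude harm on its main question; the protocol does not support that.
- **Other comparisons.** The diagnosis curve keeps everyone with a suspicious result, and completion of the work-up is compared as well. Both would tend to favor navigation in the scenarios above. This limits the damage but does not make the therapy test valid.
- **Size.** The 66% case gives navigation no effect on prompt patients, although the protocol's power calculation assumes 30 to 20 days, and it lets control diagnose none of the hard-to-reach. With the 10-day effect it falls to 8%, and the milder case turns the right way. It is an extreme of the range, not a typical value.
- **Patients with cancer at entry.** D.2.1.1 and D.2.1.2 admit pathologically confirmed, untreated cancers. Navigation cannot select on their diagnosis, so they dilute the bias. The simulations include none.
- **Intent to treat.** The section glosses the principle as analysis by assigned group whatever the degree of participation, and it names the positive-only subset openly. No patient is moved between arms. But the rule also says that all registered patients are analyzed, and on this clock they are not.
- **The alternative.** An all-patient analysis has little power under pure acceleration (about 3% to 4%). With 12 clinics, a chance difference in cancer prevalence between arms could itself produce a difference. This stands and shapes the fix.

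**Conclusion.** The point holds in a limited form. On the clock from the suspicious result, the stated log-rank test conditions on a post-randomization event that navigation is meant to change, so it is not the comparison that the section's own intent-to-treat rule requires. This is a stated rule, not a detail left to a later plan.

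The bias needs navigation to change who reaches a positive diagnosis within follow-up. If it does, the test can hide a benefit or, in stronger cases, point against navigation. The rate of significant results against navigation ran from about 0% to 66%. It depends on cancer yield, completion rates, delay in hard-to-reach patients and speed-up, none of which the protocol gives for these patients. If navigation only accelerates diagnosis, the sign is right. The simulations ignore clinic clustering.

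Two stronger readings are tempting. One is that the test will reverse the effect of navigation; the documents show only that it can. The other is that the clock from diagnosis is equally biased. It uses the same selected patients and could be distorted if hard-to-reach patients also start therapy later, but nothing in the protocol says that they do.

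**What to change.** 1. For the clock from the suspicious result, report by arm the cumulative incidence of therapy onset in all registered patients with a qualifying abnormality. Treat definitive negative resolution and death as competing events, and keep unresolved patients at risk to a common follow-up date. Give a confidence interval that respects clinic clustering.
2. Present the positive-only curves as descriptive, with no between-arm significance test for that clock. Restrict any tested comparison to patients whose cancer was confirmed at enrollment.
3. Reconcile D.4.1, which places chart abstraction at 12 months, with D.4.5, which places it about three months after diagnostic resolution or start of treatment. Under D.4.5 a patient who is never resolved has no defined follow-up.

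The cost is about a paragraph of analysis text and one added procedure. No new data are needed if the 12-month abstraction applies to everyone; otherwise unresolved patients need an abstraction date. The all-patient estimate will be low, because only patients with cancer can start therapy, has little power, and relies on similar cancer prevalence in the two arms. It should therefore be read as an estimate beside the time-to-diagnosis and completion comparisons, not as a replacement test.

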**Pinellas County Community Health Centers**

Johnnie Ruth Clarke Health Center Control

Community Health Centers Pinellas Park Intervention

Data to be collected about participating clinics:

Each clinic will be sequentially assigned a unique 2 digit ID number which will be reported in Table 1B provided to NOVA (see data dictionary).

Standard information will be collected from each clinic at the start of their participation in the project and again at the conclusion of the project. The information to be collected is described in Table 6 of the data dictionary.

D.2.1. Inclusion/Exclusion Criteria

General exclusion criteria include the following:

- Cognitively impaired
- Institutionalized
- Persons under age 18
- Previous navigation for cancer (either in PNRP or elsewhere)
- Known to be pregnant at enrollment
- Previously treated cancer (other than non-melanoma skin cancer) less than five years from diagnosis

Patients will be eligible for inclusion in the study if they receive primary medical care at one of the participating medical clinics and are noted to have a potentially cancer-related abnormality as defined below. Patients must be at least 18 years of age, but there will be no exclusion on race or income. Patients who are newly diagnosed with breast or colorectal cancer and who have not undergone any treatment will be eligible for the study.

*D2.1.1 Breast Cancer-related Abnormalities*.-- Patients having a breast-related abnormality that in the opinion of the primary physician warrants further evaluation will be eligible for inclusion. Subjects having the following breast related abnormalities will be eligible for inclusion:

- Health care provider confirmed breast mass or other abnormality suspicious for cancer prompting referral to specialist or referral for further testing
- Abnormal or incomplete mammogram (BIRADS 0, 3, 4, 5)
- Ultrasound abnormality (indeterminate or suspicious solid lesion, complex cyst, BIRADS 0,3,4,5)
- MRI abnormality (BIRADS 0,3,4,5)
- Pathologically confirmed DCIS or invasive cancer that has not been treated

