Patients having symptoms potentially related to breast cancer (abnormality noted on self-exam, breast pain, nipple discharge) will also be eligible if there are corresponding suspicious findings on clinical examination warranting referral. Patients having breast abnormalities that are fully diagnosed and treated within the primary care setting, without the need for additional evaluation, will not be eligible for inclusion in the study.

*D.2.1.2 Colorectal Cancer-related Abnormalities*.-- Patients having an abnormality potentially related to colorectal cancer, and requiring further evaluation, will be eligible for inclusion. Conditions meeting eligibility criteria include:

- Rectal bleeding in person 30 years or older with referral to specialist
- Suspicious finding on rectal exam (mass) with referral
- Abnormality on sigmoidoscopy (adenomatous/malignant polyp, mass, invasive cancer)
- Abnormal colorectal imaging (space occupying lesion by ACBE, virtual CT colonography).
- History of malignant polyp
- Positive FOBT / Guaic with referral to specialist in persons 30 years and older
- Newly diagnosed and pathologically confirmed colorectal cancer prior to treatment
- Abnormality on colonoscopy requiring additional evaluation (mass, polyp requiring excision, incomplete or unsatisfactory examination)

Patients with abnormalities that are fully diagnosed and treated in the primary care setting, without the need for additional evaluation, will not be eligible for inclusion in the study as they would have no need for navigation.

**D.3. Phase 1: To work closely with our community partners to conduct a formative evaluation of the acceptability, appeal, and appropriateness of a Patient Navigator Program.**

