###### **D.4.3 Patient Recruitment**

As described previously, seven clinics will provide the Navigator Program and five clinics will not provide the Navigator Program based on random assignment. A description of the Navigator Program to be provided at those clinics randomized to this condition follows. We will make no attempt to alter the delivery of services at those clinics not randomized to deliver the Navigator Program. Rather, we will use both observational and survey methods to characterize the processes that typically occur in these clinics once patients are identified as having a breast or colorectal abnormality. These data will be used to characterize the extent to which delivery of care differed in our two intervention conditions.

The eligibility criteria were defined in D.2.1 above. Subjects having cancer-related abnormalities will be identified by research assistants using a variety of methods. Methodologies for identifying patients will be refined and pilot tested in the project’s first year. Procedures for subject identification and recruitment will be identical for intervention and control clinics. Once identified, patients will be contacted by research assistants for recruitment into the study. Research assistants will use the following sources to identify patients:

*Appointment records*: Appointment records provide the reason for each patient’s visit and will be assessed weekly by research assistants. This information will be used to identify cancer related symptoms (i.e. breast lumps, rectal bleeding).

*Screening logs*: Participating clinics maintain screening logs to document completion of cancer screening tests such as Pap smears, mammograms, and FOBT. Research assistants will track screening logs on a weekly basis to identify patients having abnormal results on mammography or FOBT.

*Referral coordinators*: Research assistants will also make at least weekly contact with referral coordinators at each clinic to identify patients who may have been referred for cancer related problems.

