**D.4.7.a** **Outcomes**

The primary outcome for this study is the time interval (in days) between abnormal finding suspicious for cancer and resolution. The onset of this time interval is the date of the abnormality meeting eligibility criteria *(Breast:* date that abnormal mammogram/US/MRI read by radiologist, date of abnormal clinical examination finding. *Colorectal:* date of abnormal screening [date sigmoidoscopy/colonoscopy performed, date FOBT interpreted], date that abnormal imaging test read by radiologist). If more than one abnormality meets eligibility criteria the onset of this time interval will begin with the earliest abnormality. Resolution is defined as the date that a definitive diagnosis is rendered regarding the initial abnormality. For breast, resolution may be indicated by definitive pathologic/cytologic findings (for women who undergo biopsy), definitive radiologic diagnosis, or by expert opinion (from breast surgeon). For colon, resolution will be defined by the date that pathologic interpretation of a biopsy specimen is rendered (if biopsy is performed) or by the date of diagnostic colonoscopy / radiologic imaging if no biopsy is performed. If more than one abnormality meets eligibility criteria resolution will be defined for the most clinically serious abnormality diagnosed (e.g. invasive cancer>>cancers in situ>>benign pathologic findings>>definitive radiological tests)

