**E.2. Adequacy of Protection Against Risks**

*E.2.1. Recruitment and Informed Consent.--* The collaborative investigative research team brings considerable expertise working in community settings and is experienced in focus group and interview methodology. Participants will be recruited at the level of the community-based site.

Potentially eligible subjects for Phase II will be identified from intervention and control clinics using methods described in **D.4.3**. Our process of obtaining informed consent will then be as follows. Using the mailing address obtained from clinic records, we will send individuals who are eligible an introductory letter that briefly describes the study and includes a toll-free number for individuals to call within one week if they do no wish to be contacted. The mailing will also contain two copies of the study informed consent document, two copies of the HIPAA authorization, and a stamped return envelope. At least 2 weeks following the mailing of the introductory letter, potential participants will be contacted by telephone and provided a brief description of the study in their preferred language (Spanish or English). We have bilingual/bicultural research members as part of our collaborative team. Key elements in this discussion are to inform subjects of the purpose of the present study, possible risks and provisions for them, lack of guarantee of benefit, confidentiality of responses, voluntary nature of the study and the right to withdraw or refuse any questions. It will also state that if they decide not to take part that it will not affect their relationship to the health clinic. An individual who states that he/she does not know how to read well will be assisted by bilingual and bicultural members of the research team on an individual basis: the form will be read aloud to them.

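### The exploratory time-to-therapy curves count days before registration as time at risk, so time to therapy is overstated in both arms unless patients join the risk set at registration

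*Protocol*

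**What the plan says.** Protocol section D.4.7.b lists the time-to-therapy analysis among secondary analyses done in an exploratory fashion. For patients with a positive diagnosis, "we will compute Kaplan-Meier curves for time to onset of therapy for each randomized arm from both suspicious screening result and definitive diagnosis". It fixes Greenwood standard errors, Hall-Wellner 95% bands and a log-rank test at the two-sided 0.05 level. It mentions no delayed entry, left truncation or landmark.

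Section D.2.1 sets the entry condition: "Patients who are newly diagnosed with breast or colorectal cancer and who have not undergone any treatment will be eligible for the study". The breast list repeats it ("Pathologically confirmed DCIS or invasive cancer that has not been treated"), and so does the colorectal list ("Newly diagnosed and pathologically confirmed colorectal cancer prior to treatment"). The general exclusions also bar cancer that has already been treated if it is under five years from diagnosis.

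On who is analysed, D.4.7.b says that "all patients who give consent and are registered on the study will be analyzed according to the randomized group assignment".

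On the time between identification and entry, E.2.1 describes a mailed letter, after which: "At least 2 weeks following the mailing of the introductory letter, potential participants will be contacted by telephone". Section D.4.3 instead has a research assistant approach the patient with the consent form. It also says: "Procedures for subject identification and recruitment will be identical for intervention and control clinics".

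**The concern.** A patient who starts therapy after the suspicious result or the diagnosis, but before registration, can never be in the data set. A patient who is in the data set was, by the entry rule, untreated on every day up to registration. Both therapy clocks start before that date. If everyone is placed at risk from day 0, the denominator includes person-days on which an event could not have been recorded, and the fastest-treated patients are missing. The direction is fixed: the therapy rate is too low and the times are too long.

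The delivery of cancer care is part of the hypothesis in section A, and these curves are where D.4.7.b examines the start of treatment. What is at stake is whether the curves and bands describe the time to therapy in these clinics or only in patients slow enough to be enrolled untreated.

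**Working it through.** The protocol states no figure for time to therapy, so there is nothing to reproduce. The size can only be illustrated.

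**Diagnosis clock**

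Inputs, all assumed:
- exponential time from diagnosis to therapy with median m, so mean μ = m / ln 2
- a share s of analysed patients who register D days after diagnosis, untreated
- the remainder registered by the time of diagnosis

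Formulas when everyone is counted at risk from day 0:
- crude rate / true rate = μ / (μ + sD)
- proportion treated by day t (t ≥ D) = (1 − s)(1 − 2^(−t/m)) + s(1 − 2^(−(t−D)/m))

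Worked case, m = 30, s = 0.5, D = 14:
- μ = 30 / 0.693 = 43.3, and the ratio is 43.3 / (43.3 + 7) = 0.86.
- Treated by day 30: 0.5 × 0.5 + 0.5 × (1 − 2^(−16/30)) = 0.25 + 0.5 × 0.309 = 40%, against a true 50%.
- Median: 30 × log2(1 + 2^(14/30)) = 30 × log2(2.382) = 37.6 days, against a true 30.
- Simulated Kaplan-Meier with delayed entry returns 50% and about 30 days.

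Other cases with m = 30 (true value 50% by day 30):

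| Late entrants | Lag (days) | Treated by day 30, no delayed entry | Rate ratio |
|---|---|---|---|
| 25% | 7 | 48% | 0.96 |
| 25% | 14 | 45% | 0.93 |
| 50% | 14 | 40% | 0.86 |
| 100% | 14 | 31% | 0.76 |

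Over medians of 20 to 60 days, lags of 7 to 28 days and shares of 25% to 100%:
- The mildest case is m = 60, s = 0.25, D = 7: 86.6 / (86.6 + 1.75) = 0.98.
- The most severe is m = 20, s = 1, D = 28: 28.9 / (28.9 + 28) = 0.51.

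The shape of the distribution matters as well. With a gamma of mean 30 and SD 15, lags of 7, 14 and 28 days lower the rate among late entrants by 1%, 8% and 28%. Those two figures are borrowed from the protocol's screening-to-diagnosis interval, not from diagnosis to therapy.

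**Suspicious-result clock**

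Here the origin can precede registration for every patient, including one not yet diagnosed at registration, because prompt diagnosis and treatment would have kept that patient out. Assumed: result-to-diagnosis and diagnosis-to-therapy independent, each with mean 30 days; registration uniform 7 to 45 days after the result; patients already treated by then excluded. Simulated medians from result to therapy, in days:

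| Analysis | Exponential | Gamma, SD 15 |
|---|---|---|
| Truth | 50 | 57.5 |
| No delayed entry | 62 | 59 to 60 |
| Delayed entry only if diagnosed before registration | 59 | 58 to 59 |
| Delayed entry for all registered after the result | 52 | 57.5 to 58 |
| Only patients diagnosed on or after registration | 73 | 65 to 66 |

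The gamma column gives ranges where repeat runs differed. The remaining 2 days in the exponential column arise because nobody is under observation before day 7, so that curve is conditional on being untreated then.

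**Arm comparison**

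Simulated log-rank test: no effect, gamma with mean 30 and SD 15, 40 patients per arm, all of them late entrants, clustering by clinic ignored.
- lags 14 and 14 days: 5.4% rejection (5% to 6% across repeat runs)
- lags 7 and 14 days: 8.6%
- lags 7 and 21 days: 33%, falling to about 13% if half the patients are late entrants and about 8% if a quarter are

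**The case against.** The strongest reply is that the protocol is only silent. It never states that everyone is at risk from day 0, Kaplan-Meier and log-rank both allow delayed entry, and a risk-set rule for an exploratory curve is the kind of detail a statistical analysis plan supplies. This does not dispose of the point. D.4.7.b fixes the origins, estimator, standard error, bands, test and level, and that specification followed as written does not fit the entry rule in D.2.1. It does limit the weight: no stated figure is wrong.

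Several other replies stand:
- D.4.1 describes recruitment at the time of a suspicious result, and D.4.7.b focuses on abnormal mammograms, FOBT and sigmoidoscopy. Patients already diagnosed at entry may therefore be a minority.
- The two-week wait belongs to the mailed route in E.2.1. The in-person approach in D.4.3 could be faster, so the lag is not established.

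A reader might infer that the log-rank test will produce false positives, citing the 33%. The documents do not support that. It needs unequal lags and 80 late entrants, both assumed, while D.4.3 promises identical recruitment in the two arms. Equal lags are not guaranteed: in D.4.5 the navigator collects consent-time data in one arm and the research assistant in the other, and D.4.6b anticipates selective referral. Neither shows that the lag differs by arm.

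A reader might also infer that only patients diagnosed before registration need correcting. The second table shows that this leaves bias on the suspicious-result clock.

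**Conclusion.** The point holds for the secondary, exploratory time-to-therapy curves. Taken as written, D.4.7.b overstates time to therapy in both arms on both clocks. The direction follows from the entry rule and the analysis set. The size does not, because it depends on the share of late entrants, the registration lag and the therapy times, none of which the documents give. Under the assumptions shown it runs from negligible (rate ratio 0.98) to large (0.51).

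The arm comparison is distorted only if the lag or the stage at entry differs by arm; otherwise the truncation leaves the log-rank test at its level. The primary time-to-diagnosis outcome is a separate question, and nothing here bears on it. The correction is worth making before analysis, but it does not threaten the trial's main result.

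**What to change.** Add to D.4.7.b, for both therapy curves:

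- Every patient whose registration falls after the clock's origin joins the risk set on the registration date (left-truncated Kaplan-Meier), with the matching Greenwood variance and bands built from it.
- The arm comparison uses the same entry times, for example a counting-process score test.
- On the suspicious-result clock this applies to all patients registered after the result, whether or not they were diagnosed by then.

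Limiting the analysis to patients diagnosed on or after registration is acceptable only as a sensitivity analysis on the diagnosis clock, where it is unbiased if the two intervals are independent. It must not be used on the suspicious-result clock: it selects slowly diagnosed patients and was further from the truth than the plan as written. It also drops registered patients whom D.4.7.b says will be analysed.

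The cost is a sentence or two of wording. Section E.6 says consent is documented during registration, so the date should already be on file. Bands will be wider early in each curve, where few patients are at risk, and the curve cannot describe days before the earliest registration. Reporting the lag from origin to registration by arm would show whether the equal-lag assumption is reasonable. No clinical procedure changes.
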